### Responsiveness

Responsiveness is the extent to which instruments are sensitive enough to detect the smallest difference considered clinically relevant. [14] Responsiveness is a special type of construct validity.

To calculate the responsiveness of a test and to inform it to the readers is of great importance when planning a clinical trial. Indeed, the more responsive an instrument, the smaller is the number of the patients required to achieve statistical power, or alternatively, the more power is achieved with the same sample size.

Responsiveness statistics used in the analysis will the effect size, the standardised response mean, and Guyatt's method.

The effect size is the difference between the mean baseline and follow-up scores on the measure, divided by the standard deviation of the baseline scores. The effect size is defined as "small" (E-S < 0.2), "small to moderate" (E-S between 0.2 and 0.5), "moderate to large" (E-S between 0.51 and 0.79), "large" (E-S > 0.79), as suggested by Cohen.[15] The results were categorized by group of experience (novice and intermediate).

The Standardised Response Mean (SRM) is calculated as the mean change in scores divided by the standard deviation of these changes. Again the results were categorized by group of experience.[16]

The formula for Guyatt's responsiveness index is defined as Δx/√2 × MSEx, where Δx is the minimally clinically important change on the measure and MSEx is the mean squared error of the variable obtained from an analysis of variance model that examines repeated observations of the measure in clinically stable subjects.[17] Alternatively, if there are only two observations of the measure, MSEx is the standard deviation of the individual change scores in clinically stable patients (i.e., placebo-treated patients). In the present study we assume that the most stable participants were those in the expert group. This index is sometimes referred to as the modified standardised response mean, or to as the index of responsiveness.[16]

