### Administration of the test

To allow the assessment of responsiveness the test will be administered before and after the educational intervention. Repeated administration of measures, particularly those focussing on knowledge, may over-estimate the educational effect and therefore the responsiveness of the test. To minimise the recall bias two sets of test with different scenarios will be prepared. Moreover the pre-test will be administered four weeks before starting the educational module.

Novice and intermediate experience participants will be invited four weeks before starting the educational module to attend a conference about research in primary care and the importance of applying the results of this research into clinical practice. The project of validation the Fresno test will be also presented. The sessions will be decentralised by Health Regions. At the end of each session participants will receive the test (before test). The other test will be administered again on the last day of the course (after test).

The members of the expert group belong to a network of physicians who are regularly engaged in the design and conduct of clinical trials. The network holds in November its annual conference. The members who attended the conference will be asked for filing-in the test. In order to assess the equivalence of the two sets of the questionnaire, both sets will be randomly assigned among the folders distributed to the participants.

In order to assess the feasibility of the test the time required for filling-in the test will be recorded in all cases.

All the participants will be explicitly informed about the research character of the test and that participation was voluntary.

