A lack of clarity exists about the definition and adequate approach for evaluating responsiveness. Terwee et al. [16] presented an overview of different categories of definitions and methods used for calculating responsiveness identified through a literature search. Twenty-five definitions and 31 measures were found. In this study, three commonly used responsiveness indices will be estimated. Mean change scores in the Fresno test were calculated by subtracting the baseline score from the data obtained after the educational intervention: the effect size (ES) the Guyatt's responsiveness statistic (GRS), and the standardized response mean (SRM). The responsiveness of a particular measure may be influenced by the responsiveness index used, irrespective of the scope of the measure or the direction of the change. Whereas most indices use the mean change of the score over time, there are significant differences in how the standard deviations or variability in the data is used in the calculation. For example, the GRS is calculated using the standard deviation of the change scores among subjects who had stable scores (in our study the expert group), whereas the SRM uses the standard deviation of the change scores. It is therefore possible that significant differences could exist in the variability in the selected subgroups, resulting in differences in the perceived responsiveness of the measure depending upon the responsiveness index chosen.

Strength of this study is the assessment of the feasibility of the test. Feasibility concerns the ease of administration and processing of an instrument. These are important considerations for staff and researchers who collect and process the information produced by instruments.[23] Instruments that are difficult to administer and process may jeopardise the conduct of research and disrupt educational efforts. An obvious example is the additional resources required for interviewer administration over self-administration. The complexity and length of an instrument will have implications for the form of administration. Staff training needs must be considered before undertaking administration. Finally, staff attitudes and acceptance of instruments can make a substantial difference to respondent acceptability.

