The results and interpretation of this study should be considered in light of several potential limitations. Most notably, we used a before-after design. This is a shortcoming either for assessing the responsiveness of the test since we did not have the variability of a control group and we had to use as a surrogate the standard deviation of the expert group, and also for assessing the effectiveness of the course. Furthermore, the intensity of the intervention and the period chosen to minimise the recall accuracy of the participant (four weeks) may also influenced the responsiveness indices, due to the effect of external influences such as attendance to another course, looking into the main topics of the test in a book or simply by exchanging opinions and knowledge with other residents or their tutors.

Evaluation of educational interventions should not only be concerned about a gain in knowledge and skills, but also on how this gain is transferred to workplace (behavioural change) and impact on patients (health outcomes). Regarding the effectiveness of the educational intervention, assessment of EBP skills acquisition will be performed immediately after the course; so long term outcomes will not be measured. Moreover, the Fresno Test was not developed for measuring behavioural change, and the present study has not been designed either for assessing even short term behavioural change. Therefore we will not be able either to draw conclusions on behavioural change after the educational intervention.

For study-logistic reasons, only residents and tutors of Family Medicine will be included in the validation study. While it could be suggested that more similarities than differences exist between the different groups of medical residents with regard to EBP issues, the use of Fresno test in a population including residents from other specialties would require testing for validity and reliability in the specific resident's group. Levels of inter-rater reliability, internal consistency and discrimination are intimately dependent on the population which has taken the test) and it cannot be assumed that any of these key attributes can be maintained in subsequent studies with a population with a different background experience in EBP.

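### Guyatt's responsiveness index carries a √2 that should not be there when the SD of change is used, and the plan does not make clear that the experts, its stable group, yield any change scores

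*Protocol article*

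**What the plan says.** The protocol article names three responsiveness statistics: the effect size, the standardised response mean (SRM) and Guyatt's index. On the third:

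- **Formula (Responsiveness).** "The formula for Guyatt's responsiveness index is defined as Δx/√2 × MSEx", "where Δx is the minimally clinically important change on the measure". MSEx is to come from an "analysis of variance model that examines repeated observations of the measure in clinically stable subjects".
- **Two observations (Responsiveness).** "MSEx is the standard deviation of the individual change scores in clinically stable patients". Nothing is said about removing the √2.
- **Stable group (Responsiveness).** "In the present study we assume that the most stable participants were those in the expert group".
- **Who is tested twice (Participants and study description; Administration of the test).** Novices and intermediates take a test about four weeks before the course and another on its last day. For the experts the plan describes one occasion, their network's annual conference: "The members who attended the conference will be asked for filing-in the test". The two sets are allocated at random among the folders handed out there.
- **Equivalence of sets 1 and 2.** An intra-class correlation of the overall score is planned in the experts.
- **Discussion, on the choice of indices.** Guyatt's statistic is "calculated using the standard deviation of the change scores among subjects who had stable scores", with the experts given as those subjects. The numerator is presented, for all three indices together, as the mean change from baseline.
- **Discussion, limitations.** For want of a control group, "we had to use as a surrogate the standard deviation of the expert group".

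**The concern.** Two things do not fit together.

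First, the two-observation rule puts a standard deviation of differences where the formula expects a mean squared error, and leaves the √2 standing. These are different quantities in different units.

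Second, the index needs within-person variation over time in people who are not changing. The group chosen for this is the one group for which no repeat test is described. The limitations text, taken at its word, may substitute the spread between experts, which is not a measure of noise in change.

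Responsiveness is specific objective (c), and the Discussion presents it as something the original developers did not assess. The Responsiveness section also says that such figures matter for planning later trials. If a reader used the index as a standardised effect, required sample size would scale with 1/index², so an index too small by √2 would double the planned size.

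**Working it through.** The documents give no value for Δ, for any SD or for the index, so there is no figure to reproduce. The check is algebra, with assumed values for illustration only.

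**1. The two-observation denominator.** Let each stable subject have two scores with independent errors of variance MSE, any occasion effect removed. Then

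Var(change) = MSE + MSE = 2·MSE, so SD(change) = √(2·MSE).

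Hence Δ/√(2·MSE) = Δ/SD(change). The SD of change stands for the whole denominator.

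A simulation agrees (200,000 subjects, assumed between-person SD 30, assumed correlation 0.9): MSE = 89.8, √(2 × 89.8) = 13.40, and the SD of change is 13.40.

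**2. What the stated substitution gives.** With an assumed Δ = 20 and SD(change) = 13.40:

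| Reading | Index | Against the correct value |
|---|---|---|
| Δ/SD(change), correct | 20/13.40 = 1.49 | – |
| Δ/(√2·SD) | 20/(1.414 × 13.40) = 1.06 | × 1/√2 = 0.71, i.e. 29% low |
| Δ/√(2·SD) | 20/√26.8 = 3.86 | × √(SD/2) = 2.59 |

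The 29% holds whatever the data. The last factor has no fixed size: it is √(SD/2), which is 2.0 at SD 8 and 3.2 at SD 20. An index that moves with the units of the score is not a standardised index. The printed formula has no brackets, and these or a radical bar may have been lost when the text was read. The result does not depend on that, because the substitution fails under either reading.

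**3. A between-person SD as surrogate.** Let σ be the SD of expert scores on one occasion and r the correlation between two occasions, with equal variances. Then

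SD(change) = σ·√(2(1−r)), so Δ/σ = [Δ/SD(change)] × √(2(1−r)).

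| Assumed r | Factor on the index |
|---|---|
| 0.5 | √1.0 = 1.0 |
| 0.7 | √0.6 = 0.77 |
| 0.8 | √0.4 = 0.63 |
| 0.9 | √0.2 = 0.45 |

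Below r = 0.5 the factor exceeds 1 and the index is inflated. The documents give no retest or alternate-form correlation, so neither size nor direction can be fixed from them. The factor does not depend on σ or Δ.

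**4. Do expert change scores exist?** Administration of the test describes one occasion and random allocation of sets among folders, most naturally one set per expert. On that reading there is no expert change score and no repeated-measures error. The intra-class correlation between sets 1 and 2, however, needs both sets from the same person. The two sections cannot both hold unless each expert completes both sets. Even then, two sets at one sitting give an alternate-form difference, not change over the interval of more than four weeks that separates the other groups' tests.

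**5. The numerator.** The Responsiveness section uses the smallest important change; the Discussion describes observed mean change. With the same denominator these are two different indices.

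**The case against.** Several points on the other side have weight.

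- **Experts may be tested twice.** A reader might infer that experts certainly take the test once and that the index is therefore impossible to compute. The documents do not go that far. Nowhere is one set per expert stated, and the planned intra-class correlation implies paired scores. What stands is a conflict between sections.
- **The limitations wording may be shorthand.** A reader might also infer that a between-person SD will certainly be used. The sentence does not say so, and it may abbreviate the SD of change named elsewhere in the Discussion. It also openly admits the lack of a control group. The factors in step 3 therefore apply only if the single-occasion reading is the intended one.
- **The right denominator is already in the article.** The Discussion uses the SD of change without a √2, and the Responsiveness section's alternative name, the modified standardised response mean, fits that form. This makes the formula error a matter of wording, but an analyst working from the Responsiveness section would still get it wrong.
- **No value for Δ.** A condensed article may leave this to the full plan, so it is not counted. Only the two descriptions of the numerator are.
- **Limited reach.** This is one of three responsiveness statistics. The effect size and SRM use novice and intermediate data and are untouched, and no threshold or decision depends on Guyatt's index.

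**Conclusion.** The two-observation rule is wrong as written. It makes the index 29% too low under one reading and unit-dependent under the other. This is algebra and rests on no assumed value.

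Whether the experts provide change scores is unresolved: the description of test administration suggests they do not, and the planned intra-class correlation suggests they do. If a single-occasion between-person SD is used instead, the index is multiplied by √(2(1−r)), from 1.0 at r = 0.5 down to 0.45 at r = 0.9 and above 1 below r = 0.5. That range rests on assumed correlations and equal variances. The numerator is also inconsistent between sections.

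This should be fixed, but it does not threaten the study's main aim or its other two responsiveness statistics.

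**What to change.** Reconcile the Responsiveness, Administration of the test, Equivalence of sets 1 and 2 and Discussion sections on whether each expert gives paired scores. Then take one of two routes.

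- **Experts are not retested.** Remove Guyatt's index from the Abstract, the Responsiveness section and the Discussion, and report the effect size and SRM only. Do not use a between-person SD as a surrogate. The cost is wording.
- **Experts are tested twice.** Space the tests over an interval comparable to the pre/post interval of the other groups, with set order randomised. Define the index as Δ/SD(change in experts), without a further √2, and use one definition of Δ throughout. The paired scores would also supply the intra-class correlation between sets. The cost is a second test for the experts, which may reduce their response.

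If experts complete both sets at one sitting, report the result as alternate-form difference only and label it so.

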### Internal consistency

Internal consistency refers to the extent to which individual items of the instrument are consistent to one another and reflect an underlying scheme or construct. For internal consistency reliability, two measures will used: Cronbach's alpha and corrected item-total correlations.

Cronbach's alpha coefficient is used to evaluate the internal consistency between the questionnaire elements. Cronbach's alpha coefficient measures how well a set of items (or variables) measures a single uni-dimensional latent construct. Achievable values for Cronbach's alpha range from 0 (signifying no correlation) to 1 (indicating identical results). When data have a multidimensional structure, Cronbach's alpha will usually be low. Technically speaking, Cronbach's alpha is not a statistical test – it is a coefficient of reliability (or consistency).[18]

The reliability of an instrument has implications for whether it is suitable for application in group or individual evaluation. For the evaluation of individuals high levels of reliability, above 0.90, have been recommended. For group comparisons, levels over 0.70 are recommended. In the present study, values greater than 0.70 will be considered evidence of internal consistency.[19]

Pearson's correlation coefficient will be also calculated to assess the relation between an individual item and the instrument as a whole omitting that item (corrected item total correlation) to identify items contributing to a low reliability. Corrected item-total correlations indicate the extent to which each item relates to the construct measured by the total score. Correcting the total score by removing the item of interest prevents spuriously high values due to item overlap; values greater than 0.30 will be considered evidence of internal consistency. [20]

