**Item difficulty **(relative difficulty of each item)	% of candidates who answer achieve a passing score	Not given	Ranged from moderate (73%) to difficult (24%); no easy items

**Item discrimination **(ability of each item to discriminate between those with overall high scores and those with overall low scores)	Item discrimination index (ranges from -1.0 to 1.0)	Not given	Ranged from 0.41 to 0.86, no items had negative or weak discriminations

**Construct validity **(evidence that the test measures the construct it intends to)	Mean scores of experts and novices compared by *t *test	Significant difference, higher expert scores than novices	Significant difference, higher expert scores than novices

*Adaptation of Ramos et al[9]

The primary aim of the study is the translation of the Fresno questionnaire into Spanish and its subsequent validation to ensure the equivalence of the Spanish version against the English original.

The specific objectives are: (a) To translate the test into Spanish using the back translation method; (b) To assess the construct validity of the test comparing the scores achieved by tutors with formal methodological training in EBP, the scores of a group of family medicine residents before they have had any formal training in EBP, and finally the scores of a group of family medicine residents with intermediate experience (training) in EBP; (c) To assess the responsive validity (change in knowledge and skills) of the test after a short course in EBP carried out in a group of family medicine residents; (d) To assess the reliability of the test by measuring the internal reliability (degree to which all test questions on the test measure a single construct), the inter-rater reliability (degree to which two scorers rate a single performance similarly), the intra-rater reliability (degree to which onescorer rate a single performance similarly); (e) To assess the feasibility of implementation by reporting the time required administering the test and reporting the time required scoring the instrument.

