## Discussion

Reliability, validity and responsiveness are context-specific attributes, and an instrument that has demonstrated satisfactory measurement properties in one population is not necessarily appropriate for use in other populations.[22] The validation of the Fresno questionnaire into different languages, professional groups, and cultural settings, will enable the generalisability of the test, as well as allowing comparisons between countries and the evaluation of different teaching methods.

Ramos et al. [9] pointed out that there are limitations to the validity, reliability, and general utility of the Fresno test. The reason being the groups they used to develop and validate the test, which probably represented the extremes of proficiency, leaving the middle ground relatively under-represented. The properties of the test may change when it used to assess groups of people that are more representative of the full range of proficiency in EBP. In the present study the inclusion of the group with intermediate experience may represent a wider range of proficiency in EBP. the validation of the Fresno questionnaire into Spanish, in a population with a different background of experience in EBP than the population recruited by Ramos et al [10], will enable the generalisability of the test, as well as allowing comparisons between countries and the evaluation of different teaching methods.[9]

The goals of the instrument include differentiating between people who are knowledgeable and skilled in EBP from those who do not at a point in time (a discriminative instrument) as well as measuring how much knowledge and skills have changed during a period of time (an evaluative instrument). In both cases the instrument must have a high ratio of signal to noise (reliability and responsiveness, respectively) and be valid.

Ramos et al. [9] did not perform an assessment of the responsiveness of the test. In the present study the group of novices, as well as the group of intermediate experience received an educational intervention on EBP about four weeks after completing the pre-test. The last day of the course the test was administered again allowing for the assessment of the responsiveness of the test. Since there are two groups with different experiences it could be expected that the responsiveness would be different, fostering the generalisability of the result.

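### Cronbach's alpha above 0.70 cannot show that all items measure one construct, so the single-construct part of objective (d) needs a dimensionality analysis

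*Protocol article*

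**What the plan says.** In the Background of the protocol article, objective (d) sets out to assess "the internal reliability (degree to which all test questions on the test measure a single construct"). Table 1 uses the same definition and names Cronbach's alpha as its measure, with 0.88 for the English Fresno test.

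The Internal consistency section says that "Cronbach's alpha coefficient measures how well a set of items (or variables) measures a single uni-dimensional latent construct" and adds that "When data have a multidimensional structure, Cronbach's alpha will usually be low". It then sets the mark: "In the present study, values greater than 0.70 will be considered evidence of internal consistency". The only other check in that section is a corrected item-total correlation above 0.30. The article describes no factor analysis or other check of dimensionality.

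The Background also says that the test was built to cover all domains of evidence-based practice: framing a question, choosing a design, searching, appraising relevance and validity, and judging the size and importance of results.

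**The concern.** Read together, objective (d), Table 1 and the Internal consistency section make alpha above 0.70 the evidence that the items measure one construct. The sentence on multidimensional data supplies the missing step: if several dimensions usually give a low alpha, an alpha that is not low points to one dimension. That step is unsafe. Alpha is a function of the number of items and their average correlation, and very different structures share the same average.

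This matters for a test that spans several skills and is reported as one overall score. If the skills form separate dimensions, the study could still pass both internal-consistency marks and report that the Spanish test measures one thing. Users would then take the total score as a measure of a single competence on evidence that cannot separate one construct from two.

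**Working it through.** The article derives no figure here; 0.70 is a cited threshold, so there is nothing to reproduce. The check is whether data with more than one construct can pass both marks.

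**Inputs.** From the article: alpha above 0.70, item-total correlation above 0.30, and the original's alpha of 0.88. Assumed, because the article does not state them: the number of items *k* (12 as the main case), equal blocks of *h* items with correlation *r* inside a block and 0 between blocks, and sample sizes of 100 and 200.

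**Formulas.** With *S* the sum of all entries of the item correlation matrix:

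- standardised alpha = k/(k − 1) × (1 − k/S)
- corrected item-total correlation = (h − 1)r / √(S − 1 − 2(h − 1)r)

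**Two unrelated constructs, 12 items (two blocks of six), S = 12 + 2·6·5·r.**

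- r = 0.4: S = 36. Alpha = 12/11 × (1 − 12/36) = 0.73. Item-total = 2/√31 = 0.36.
- r = 0.5: S = 42. Alpha = 12/11 × (1 − 12/42) = 0.78. Item-total = 2.5/√36 = 0.42.

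Both marks are passed. In simulated samples at r = 0.5, alpha exceeded 0.70 in 96% of samples of 100 and in 99.6% of samples of 200.

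**One construct with the same average correlation.** In the r = 0.5 case the mean inter-item correlation is 30/132 = 0.227. If all 12 items instead correlate uniformly at 0.227, as under a single factor, S = 12 + 132 × 0.227 = 42 again. Alpha is 0.78, and the item-total correlation is (11 × 0.227)/√36 = 0.42. The two planned statistics are identical for one construct and for two unrelated ones.

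**Where alpha does stay low (blocks uncorrelated).**

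| Items and blocks | r | Alpha |
|---|---|---|
| 8 items, 2 blocks | 0.5 | 0.69 |
| 12 items, 3 blocks | 0.5 | 0.66 |
| 12 items, 3 blocks | 0.6 | 0.70 |
| 12 items, 4 blocks | 0.5 | 0.55 |
| 12 items, 6 blocks | 0.5 | 0.36 |

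With two blocks, alpha passes 0.70 once r exceeds about 0.70 (k = 6), 0.36 (k = 12), 0.24 (k = 18) or 0.19 (k = 24). At those points the item-total correlation is 0.43, 0.33, 0.28 and 0.25, so the 0.30 rule catches some cases with 18 or more items but not those with 12 or fewer.

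**Distance from the original.** For an observed alpha of 0.71 with 12 items, the 95% confidence interval from the Feldt F distribution is 0.62 to 0.79 at n = 100 and 0.65 to 0.77 at n = 200. Such a result passes the mark, yet 0.88 lies outside both intervals. This treats 0.88 as known without error.

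**The case against.** The strongest reply has four parts.

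- **The sentence is hedged.** It says usually, and a counterexample with two blocks does not refute that. With many uncorrelated blocks or few items alpha is indeed low, and the Background lists about five kinds of task. This stands: the sentence is not flatly false. It is still too weak a premise for the inference, since plausible structures pass. If the domains correlate modestly, alpha rises further: six blocks of two with r = 0.5 inside and 0.2 between give S = 12 + 12·0.5 + 120·0.2 = 42, so alpha is again 0.78. Those items share some common variance, but alpha does not say whether one dimension suffices.
- **The literal label is internal consistency, not one construct.** True; the single-construct reading comes from the article's own definitions in objective (d), in Table 1 and of alpha itself. Those definitions leave little other reading. Construct validity has its own section, but comparing known groups and relating scores to hours of exposure does not address dimensionality.
- **Equivalence.** A reader might infer that an alpha of 0.71 would be declared equivalent to the original, because the primary aim is "to ensure the equivalence of the Spanish version against the English original". The document does not support that. It gives 0.70 as the level for group comparisons, never names it an equivalence criterion, and seeks conceptual equivalence through back-translation. The Discussion adds that the original was validated in groups that were probably at the extremes of proficiency, and that internal consistency depends on the population. A lower alpha could therefore reflect the participants and not the translation, so a formal margin against 0.88 would be a debatable test.
- **Individual use.** A reader might also infer that 0.70 is offered as enough to judge single trainees, since one stated goal is "differentiating between people who are knowledgeable and skilled in EBP from those who do not". The section itself says otherwise: "For the evaluation of individuals high levels of reliability, above 0.90, have been recommended". No passage claims that 0.70 establishes fitness for individual decisions.

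**Conclusion.** The point holds in a limited form. The two internal-consistency checks cannot support the single-construct part of objective (d). Under an assumed 12 items, two unrelated constructs with within-block correlations of 0.4 to 0.5 give alpha of 0.73 to 0.78 and item-total correlations of 0.36 to 0.42, which pass both marks and match what a single factor with the same mean correlation would give. The size rests on the assumed number of items, number of blocks and correlations; with 8 items, or with four or more uncorrelated blocks of 12 items at r = 0.5, alpha falls short of 0.70.

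Alpha remains usable as a reliability coefficient, which the section also calls it, and no sample or estimate is wrong. The documents do not support the stronger readings that the plan uses 0.70 to declare equivalence or to license decisions on individuals. It is enough that the report should not draw equivalence from that mark.

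**What to change.** In the Internal consistency section, delete or correct the sentence on multidimensional data and describe alpha as a reliability coefficient only. Base any single-construct statement under objective (d) on a factor analysis with parallel analysis of the pre-test item scores, which the study collects in any case. Report alpha with a 95% confidence interval beside the original's 0.88, descriptively, and repeat the Discussion's own caution that alpha depends on the population tested. State that alpha above 0.70 is not taken as showing equivalence with the English version; no formal margin is needed.

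The cost is a little more analysis and no new data. Factor-analytic precision will be limited if the sample is small, and the conclusion may be less favourable than a pass on alpha alone.
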